#### Biospecimen collection and laboratory examination

Children with overweight or obesity and some of the participants with normal weight (matched for sex and age) will be recruited to collect venous blood at baseline; urine samples will be collected at baseline and 1-year follow-up. A total of 2 ml and 1 ml venous blood will be collected in coagulation and anticoagulation collection tubes, respectively. These participants will receive a vacuum stool collection tube and 15-ml urine tube 1 day before physical inspection, and they will be asked to collect stool and urine samples in the morning and take them to the researchers at school on the physical inspection day. All of the biological sample will be transferred with an ice bag to a local collaborating hospital within 2 hours after collection. Blood samples in coagulation collection tubes will be centrifuged to extract serum. Then, all biospecimens will be transferred with dry ice to the Biobank of Shanghai Children’s Medical Center and stored at − 80 °C.

Part of the serum sample will be used to test follicle-stimulating hormone (FSH), luteinizing hormone (LH), and estrogens (E2) in girls and testosterone (T) in boys; the residual serum will be used to test leptin, kisspeptin, and ghrelin levels. A whole-blood sample will be used to analyze the pleiotropic genes of precocious puberty and obesity.

Simultaneous quantification of 64 steroids, including EED in pediatric plasma and urine by LC–MS/MS. Using the SNaPshot technology of ultra-high throughput SNP typing to detect genetic markers, thousands of SNP loci can be detected in each reaction. ABI3730XL sequencer was used for simultaneous detection of several samples.

#### Children’s health and family environment questionnaire

i.Basic information of children, including age, sex, birth status, siblings, adoption, and physical and sexual development.ii.Basic Information of Children’s Parents and Family Environment, including parents’ educational level, occupation, weight status and marital status; and family annual income, and address.iii.A sleep pattern questionnaire, including wake-up time, bedtime, and daytime napping time on workdays and weekdays and chronotype (morning, intermediate, or evening type), is used to document the sleep/wake patterns of children in the past week.iv.The dietary habit questionnaire, which consists of food consumption frequency, frequency of consuming plastic or tin packaged products, and frequency of consuming take-out food during the past week [36, 37].v.Physical activity habits are assessed using the Physical Activity Questionnaire to record the days and times of high-, moderate-, and low-intensity activities of children during the past week [38].vi.Items from the Pubertal Development Scale (PDS) are also adapted to assess puberty development, which is indicated by 4 items (growth spurt, pubic hair, skin changes, and breast development) in girls and by 5 items (growth spurt, pubic hair, skin changes, voice breaking, and facial hair) in boys. For each, the parent rates his or her child’s development as “has not started yet,” “has barely started,” “has definitely started,” “seems complete,” or “unclear.” For each adolescent, the PDS score is the mean of the sum of items [39].

### Data analysis

Categorical variables will be reported as the number and percentage and analyzed by a chi-square test to compare the distribution between groups. The *t*-test, analysis of variance, and Wilcoxon rank-sum test will be used to compare the differences in distribution of continuous variables, which will be described by mean ± standard deviation (*SD*) for normal data or median with interquartile range for non-normal data.

Based on the discovered pleiotropic genes and obesity-related risk loci (SNPS), we will examine the distribution of gene polymorphisms (SNPS). For obesity-related SNPs of these genes, Effect size Weighting was carried out according to the method reported by Speliotes EK et al. [40], and then genetic risk scores (GRS) will been calculated using the method established in our previous study [41].That is, the number of effective Allele genes (Allele) was calculated, then the weighted value was multiplied, and finally the combined GRS of SNPs of all candidate genes in this study was accumulated.

The effects of exposure factors on outcomes will be evaluated after adjusting confounding factors using logistic regression or multiple linear regression. To analyze whether there is a linear trend of GRS among four groups: children with normal weight and normal puberty, with normal weight and precocious puberty, with overweight/obesity and normal puberty, and with overweight/obesity and precocious puberty, the Cochran–Mantel–Haenszel Trend Test will be used. After 3 years’ follow-up, a causal relationship model between exposure factors and outcomes will be established by using Mendelian randomization (MR) and Egger’s regression models and assessed by sensitivity analysis. Statistical analyses will be performed by using IBM SPSS, STATA and R statistical packages. and the level of significance will be set at *p* < 0.05.

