Previous studies on the relationship between obesity and precocious puberty have mostly been cross-sectional studies, with few studies on pleiotropic genes of obesity and puberty. To explore the relationship between obesity and puberty development, this prospective cohort study will investigate the genetic, parental, social and family environment, lifestyle, and other determinants of puberty development. This protocol describes an overview of the design and methods of this cohort study, which is funded by the National Natural Science Foundation of China (grant number 81872637). The study objectives are as follows: I) analyzing the incidence of precocious puberty in the general population in China, examining the direct effect of childhood obesity on precocious puberty; II) exploring the relationship between prepuberty obesity and its risk genes and precocious puberty; III) determining the relationship between prepuberty obesity and its risk genes and hormone levels among children with precocious puberty; and IV) analyzing the interaction effect between genes and environmental factors on precocious puberty.

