## Methods

### Study design, setting, and participants

#### Study design and sampling

This study is a prospective multi-center cohort study sponsored by the Shanghai Children’s Medical Center affiliated to the School of Medicine, Shanghai Jiao Tong University and performed in three cities in southern, central, and northern China, namely, Zhongshan, Guangdong Province, Qufu, Shandong Province, and Dalian, Liaoning Province. According to socioeconomic level and geographical distribution, the districts of Zhongshan, Qufu, and Dalian are stratified into urban districts in the central area and suburban districts in suburban areas. Using a stratified cluster random sampling method, districts and schools will be selected according to geographical location and school size by a random number generator. Grade 1, 2, and 3 children (6 to 10 years old) from primary schools will be included in this study. However, participants with overweight or obesity with a history of hormone treatment in the past 6 months as reported by parents in the questionnaire will be excluded.

We will carry out a nested case-control study, which will be nested in this cohort study. Participants in case-control study will be enrolled in four groups: children with normal weight and normal puberty, with normal weight and precocious puberty, with overweight/obesity and normal puberty, and with overweight/obesity and precocious puberty. And they will be measured body composition, collected venous blood, and stool at baseline, and collected urine samples at baseline and follow-up periods.

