#### Sample size

Based on the formula for calculating the sample size of a cohort study at one-side significance level: [22].$$N={\left[\frac{u_{\alpha}\sqrt{2\overline{p}\left(1-\overline{p}\right)+}{u}_{\beta}\sqrt{p_1\left(1-{p}_1\right)+{p}_2\left(1-{p}_2\right)}}{p_1-{p}_2}\right]}^2$$

According to the previous studies, the prevalence of precocious puberty was 4.85% (*P*_2_) and 8.43% (*P*_1_) of children aged 7–10 years with normal weight and overweight, respectively [12, 23]. A type I error (*α*) of 0.05, u_0.05_ = 1.96;, β = 0.10, u_0.10_ = 1.28; and a loss of follow up rate of 15%, a total of 4152 children will be required in each center. Finally, inverse-variance weighting (IVW) methods will be used to adjust the sample size.

Based on the SNP gene differences between different groups reported in the literature, Quanto 1.2.4 software (John Morrison, W. James Gauderman 2009, University of Southern California) was used to estimate sample sizes for each group. According to the previous pre-experimental results of obesity study showed that the allele frequency was 0.30 and the minimum allele frequency (MAF) was 0.10 using Additive Genetic Model (ADD), the type I error (α) of 0.05, the actual Power is 0.80, we need average of 800 participants per group and 3200 cases for four groups. Cases among four groups will be controlled by sex and age.

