## Discussion

In this protocol, we described the study design, data collection methods, and analysis of a prospective cohort study in a population-based primary school children. According to the geographical distribution, we chose three cities in northern, central, and southern China and did our best to carry out this study to ensure the representativeness of the population. Students in grades 1 to 3 in randomly selected primary schools are expected to represent local school-age children.

By collecting information on factors such as children’s family environment, lifestyle, and genes, this study will analyze the effect of these factors on children’s physical development from the perspectives of heredity and environment. As a longitudinal study, this study will start earlier in development than previous studies to capture the impact of early childhood experiences on puberty development. Puberty is defined through visual and palpation inspection by a clinical doctor combined with ultrasonic diagnostics; previous studies have depended on self-reports or clinical palpation by non-professional volunteers, which are less sensitive and precise measurements, especially for breast development assessment among obese girls, which may lead to overestimating the precocious puberty detection rate among obese girls, since it is difficult to distinguish adipose tissue and breast tissue, so we will use ultrasonic examination in this study. Although the relationship between obesity and the sexual development of children has been confirmed in both genders by many earlier studies, due to the racial differences in the influence of obesity on sexual precocity, the relationship between obesity and early development is controversial among boys. Through this prospective cohort study, we will further investigate the relationship between obesity and development among Chinese mainland children.

To expand the previous research on puberty development, this study starts from the gene pleiotropy of obesity and takes the lead in studying the influence of the genetic polymorphism of obesity on precocious puberty. Although studies on genetic polymorphism of obesity or precocious puberty in girls have been performed previously, there has been no report on the combination of the two phenotypes, which is expected to reveal the genetic mechanism of the association between childhood obesity and precocious puberty.

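### Districts and schools are the sampling units, but the size formula and named analyses treat children as independent; intervals for incidence and school-shared exposures will be too narrow

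*Protocol article*

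**What the plan says.** **Sampling.** Study design and sampling divides each of the three cities into urban and suburban districts and continues: "Using a stratified cluster random sampling method, districts and schools will be selected according to geographical location and school size". The Discussion confirms who is enrolled: "Students in grades 1 to 3 in randomly selected primary schools are expected to represent local school-age children". The cohort is therefore grades 1 to 3 of sampled schools, not whole schools.

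**Size.** Sample size introduces its calculation with "Based on the formula for calculating the sample size of a cohort study at one-side significance level" and prints the formula for two independent proportions. It gives no ICC, cluster size or design effect. The one adjustment it names is inverse-variance weighting, which as described does not correct for clustering.

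**Analysis.** Data analysis says categorical variables will be "analyzed by a chi-square test to compare the distribution between groups". It adds the t-test, analysis of variance, the Wilcoxon rank-sum test and a Cochran-Mantel-Haenszel trend test. For adjusted effects: "The effects of exposure factors on outcomes will be evaluated after adjusting confounding factors using logistic regression or multiple linear regression". It names no mixed model, GEE, cluster-robust variance or survey method, and no school, stratum or city term.

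**Targets.** Objective I is "analyzing the incidence of precocious puberty in the general population in China". The primary outcome, under Sexual development assessment, is the difference in incidence between normal-weight and obese children. Objective IV adds environmental factors.

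**The concern.** Pupils of one school are likely to resemble each other. They share a neighbourhood and, in part, diet and lifestyle, which the study itself treats as determinants of puberty. They are also examined at school by clinicians from the local collaborating hospital, on an outcome that rests on inspection and palpation. A common examiner threshold is plausible, although the article does not say how examiners are assigned.

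With such correlation, a formula for independent children overstates the information in the sample. The effect depends on the quantity:

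- A plain rate, such as incidence, takes the full design effect.
- An exposure that is constant within a school also takes the full effect, and one that is partly shared takes part of it.
- An exposure that varies between pupils of the same school, such as weight status or genotype, takes little of it.

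At stake is the precision claimed for objective I, a headline result, and for some of the environmental associations.

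**Working it through.** **1. The plan's own size figure.** Inputs from Sample size: P1 = 0.0843, P2 = 0.0485, u values 1.96 and 1.28, loss 15%. The mean proportion is 0.0664.

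N per group = [(1.96 × √(2 × 0.0664 × 0.9336) + 1.28 × √(0.0843 × 0.9157 + 0.0485 × 0.9515)) / 0.0358]² = 1013.4.

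Two groups need 2027, and 2027 / 0.85 = 2385. The stated requirement is 4152 per centre, and 4152 / 2385 = 1.74. The printed formula contains no clustering term and does not give the stated number. The text does not explain the excess.

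**2. Incidence.** Design effect = 1 + (m − 1) × ICC, and the interval widens by its square root. Pupils per school (m) and ICC are assumptions. For scale, take 4152 × 0.85 = 3529 completers in one centre and a rate of 4.85%, the article's figure for normal-weight children. The 95% half-width under independence is 1.96 × √(0.0485 × 0.9515 / 3529) = 0.71 percentage points.

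| m | ICC | Design effect | Interval factor | Half-width (points) | Coverage of the nominal 95% interval |
|---|---|---|---|---|---|
| 50 | 0.005 | 1.245 | 1.12 | 0.79 | 92% |
| 100 | 0.01 | 1.99 | 1.41 | 1.00 | 84% |
| 200 | 0.02 | 4.98 | 2.23 | 1.58 | 62% |

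An exposure constant within a school takes the same factors. Larger assumed values give more: 300 pupils and ICC 0.05 give 1 + 299 × 0.05 = 15.95, a factor of 4.0.

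**3. Obesity contrast.** For an exposure that varies within schools, design effect ≈ 1 + (m − 1) × ICC of exposure × ICC of outcome.

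- If obesity prevalence does not differ between schools, the exposure ICC is 0 and the design effect is 1.00.
- With m = 200, outcome ICC 0.02 and exposure ICC 0.05, it is 1 + 199 × 0.02 × 0.05 = 1.199, a standard-error factor of 1.09.
- With m = 300 and both ICCs 0.05, it is 1.75, a factor of 1.32.

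A simulation of 18 schools with 200 children each (school SD of the outcome on the logit scale 0.4 to 0.7) agrees. The ratio of true to naive standard error was 1.00 to 1.01 when obesity prevalence did not vary by school, with type I error about 5%. It was 1.02 to 1.11 when prevalence did vary, with type I error 5.8% to 7.7%.

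**4. Power of the contrast.** Apply the Table 3 shares (21.79% overweight or obese, 62.57% normal weight) to 3529 completers. This gives about 769 against 2208 children in one centre.

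- Independent children: two-sided power 93.5%.
- Simulated worst factor of 1.11 (design effect 1.23): about 88%.
- Full design effect of 1.99: 71%. With three such centres pooled: about 99%.

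**The case against.** **The article may leave the variance method to a fuller plan.** Naming logistic regression does not exclude cluster-robust errors. This limits the point but does not remove it. The article states a clustered design, an independent-sample size formula and a list of independent-observation methods, and these do not match.

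**Not every interval is affected.** A reader might infer that all confidence intervals, including the one for the primary contrast, will be clearly too narrow. The documents do not support that. Weight status and genotype vary between pupils of a school, and the expected effect is nil to modest.

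**Power.** A reader might also infer that power collapses, for example to 71%. That figure applies the full design effect to an exposure that varies within schools, and to one centre alone. Data analysis does not say that the primary contrast is tested centre by centre.

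**The final size may contain an allowance.** Because 4152 exceeds the formula's 2385 without explanation, a hidden allowance for clustering cannot be ruled out. Nothing in the text attributes the excess to clustering either. What can be said is that the printed formula has no such term.

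**Urban share.** Table 3 shows 77.34% urban children. One might infer a biased incidence, but the table covers two of the three cities, and the article gives no population share or sampling fraction. Selection by location and school size does not exclude proportional sampling.

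**Size of the effect.** Pupils per school and ICC are assumed. This objection stands, so the design effect is a range and not an estimate.

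**Conclusion.** The point holds for objective I and for exposures shared within a school. Followed as written, the analysis understates their uncertainty. Under 50 to 200 pupils per school and an ICC of 0.005 to 0.02, intervals should be about 1.1 to 2.2 times wider. Both inputs are assumptions. The direction follows from any positive within-school correlation.

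The obesity contrast and the gene analyses are affected little or modestly. A loss of the stated power, a final sample that lacks any allowance, and an urban bias in the incidence are not shown.

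**What to change.** - **Incidence:** estimate it with design-based variances. Use the first-stage sampling unit as the cluster, district or school according to how the draw was made, and city by urban/suburban as strata. Add inverse-selection weights if selection was not proportional.
- **Regressions:** fit them as GEE, mixed-effects or cluster-robust models by school, with fixed effects for city and district type.
- **Group comparisons:** replace the plain chi-square test with a design-adjusted version.
- **Reporting:** state the number of schools, the pupils per school and the observed ICC. Say how 4152 was reached and whether it includes a design effect.

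**Cost:** wider intervals and a little more analysis work, in software the article already names. No further children or procedures are needed. The school identifier must be kept in the analysis data; the article does not list it among the recorded items, though it should be known from the sampling. If weights are needed, the selection probabilities must be recovered from the draw.

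### The planned trend test of the obesity-SNP risk score across four weight-by-puberty groups can be significant with no link to precocious puberty, so by itself it is not evidence of one

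*Protocol article*

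**What the plan says.** The relevant text is in the Data analysis section of the protocol article.

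- **Risk score.** It is an obesity score: "For obesity-related SNPs of these genes, Effect size Weighting was carried out". Weighted effect-allele counts are then summed over the candidate genes.
- **Question and groups.** The stated question begins "To analyze whether there is a linear trend of GRS among four groups: children with normal weight and normal puberty" and continues "with normal weight and precocious puberty, with overweight/obesity and normal puberty, and with overweight/obesity and precocious puberty". These four groups are a 2 x 2 cross of weight status and puberty status.
- **Test.** The text says "the Cochran–Mantel–Haenszel Trend Test will be used". It gives no group scores and no reason for the order.
- **Level.** The general significance level is p < 0.05.
- **Group size.** The Sample size section says "we need average of 800 participants per group and 3200 cases for four groups", with "the type I error (α) of 0.05, the actual Power is 0.80". It states no risk-score difference and no power for the trend test.

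The same Data analysis section also plans confounder-adjusted logistic or linear regression and, after three years of follow-up, Mendelian randomization with Egger regression.

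**The concern.** A linear trend test needs ordered groups. Children with neither condition and children with both are plausible extremes. Nothing ranks a normal-weight child with precocious puberty below an overweight child with normal puberty. The listed order therefore fixes, without saying so, how much weight status and puberty status each count in the test.

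A score made from obesity SNPs can be expected to differ by weight. If it does, the trend statistic can be significant even when the score is unrelated to puberty at a given weight. Objective II in the Background section concerns obesity risk genes and precocious puberty. A reader who took a significant trend as support for that objective could be looking at nothing more than obesity genes relating to obesity.

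**Working it through.** **Inputs from the protocol.** Four groups in the listed order; on average 800 per group; level 0.05. The plan's total reproduces: 4 x 800 = 3200. The 800 itself cannot be re-derived because no effect size is stated, and it is used here only as the group size.

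**Assumptions.** Scores 0, 1, 2, 3 in the listed order; exactly 800 per group; two-sided 0.05 (sidedness is not stated for the genetic calculation); risk score roughly normal with within-group SD 1; no adjustment for sex and age. The risk-score difference by weight (dO) or by puberty (dP) is not given, so a range is shown.

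**Step 1: what the scores encode.** Let O = 1 for overweight/obesity and P = 1 for precocity. The groups are (O,P) = (0,0), (0,1), (1,0), (1,1), and 0, 1, 2, 3 is exactly 2 x O + P. With equal groups the variance of 2O is 4 x 0.25 = 1.00 and that of P is 0.25. Obesity therefore carries 1.00/1.25 = 80% of the score variance and puberty 20%.

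**Step 2: slope and standard error.** The centred scores are -1.5, -0.5, 0.5, 1.5, with sum of squares 5.

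- Obesity-only difference d (means 0, 0, d, d): slope = (0.5d + 1.5d)/5 = 0.4d.
- Puberty-only difference d (means 0, d, 0, d): slope = (-0.5d + 1.5d)/5 = 0.2d.
- SE of the slope = 1/sqrt(800 x 5) = 1/sqrt(4000) = 0.0158 SD.

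**Step 3: rejection probability of the trend test.** z = slope/SE.

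| Difference (SD) | Obesity only: z | Rejects | Puberty only: z | Rejects |
|---|---|---|---|---|
| 0.05 | 1.265 | 24% | 0.632 | 10% |
| 0.10 | 2.530 | 72% | 1.265 | 24% |
| 0.15 | 3.795 | 97% | 1.897 | 48% |
| 0.20 | 5.060 | 99.9% | 2.530 | 72% |

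Simulation with 3000 runs agrees: 72% and 99.9% for obesity-only differences of 0.10 and 0.20 SD, and 25% and 71% for puberty-only differences of the same size.

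**Step 4: dependence on the order.** Swapping the two middle groups makes the score O + 2P and exchanges the two halves of the table. An obesity-only difference of 0.20 SD then rejects 72% of the time instead of 99.9%. Either order mixes the two effects.

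**Step 5: cancellation.** With dO = 0.10 and dP = -0.20, the slope is 0.4 x 0.10 - 0.2 x 0.20 = 0. The test then rejects 5% of the time although both effects are real.

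**Step 6: the alternative.** Take the puberty difference within each weight stratum and average the two. Each difference has variance 2/800, so the average has variance 1/800 and SE 0.0354. At dP = 0.10, z = 2.83 and power is about 81%, against 24% for the trend test. When only obesity matters, rejection stays at the nominal 5% (simulated 4.4% to 4.6%).

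**The case against.** **Other planned analyses.** The trend test does not stand alone. Adjusted regression and Mendelian randomization with Egger regression are also planned, and the Discussion assigns pleiotropy and the mediating role of obesity to the latter. This stands as far as it goes: those analyses could address the link. But the regression sentence speaks only of exposures and outcomes and does not name a weight-adjusted test of the risk score against puberty. Neither analysis changes what the stated trend test measures.

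**Stronger readings.** A reader might infer any of the following, and the documents do not support them.

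- *The four groups have no order at all.* Only the middle pair is unordered; neither condition and both conditions are reasonable extremes.
- *The trend will be significant, and because of obesity alone.* That depends on a risk-score difference the protocol does not give. At 0.05 SD the probability is only 24%, and a puberty effect also enters the statistic.
- *The study cannot show a genetic link with precocity.* The limit applies to the trend test read by itself, and that test is weak for puberty, not blind to it.
- *The test cannot handle a continuous score.* The one-degree-of-freedom correlation form accepts numeric scores.
- *The 20 SNPs in Table 2 will each be judged at 0.05 without correction.* The section says only "the level of significance will be set at" p < 0.05 in general. Multiplicity across SNPs is a separate matter, commonly left to an analysis plan that is not shown.

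**Conclusion.** The point holds in this form: the trend test confounds weight status with puberty status, and a significant result, read alone, is not evidence that the risk score is related to precocious puberty. With no puberty effect, the chance of a significant trend runs from about 24% to 99.9% over assumed weight differences of 0.05 to 0.20 SD. For a real puberty-only difference of 0.10 SD, the test has about 24% power where a within-stratum contrast has about 81%.

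These figures rest on scores 0 to 3 in the listed order, equal groups of 800, a roughly normal risk score and a two-sided 0.05 level. The structural argument, that the score is a weighted sum of two different conditions, does not depend on the assumed differences.

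This should be fixed, but it does not touch the primary outcome, which is the difference in incidence of precocious puberty between normal-weight and obese children. The trend test is a secondary genetic analysis.

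**What to change.** Replace the trend test, or keep it as description only with no inferential claim. Test the association between risk score and puberty with weight status in the model, in one of two ways:

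- a linear model of the risk score on weight group and puberty group as separate main effects; or
- logistic regression of precocity on the risk score plus weight group.

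Adjust either model for age, sex and city.

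Test the weight-by-puberty product term separately, or use centred coding. With 0/1 coding and the product term in the model, the puberty coefficient describes normal-weight children only. Its SE is then sqrt(2/800) = 0.05, so at 0.10 SD z = 2.0 and power is about 52% instead of 81%.

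The cost is analysis wording only. No extra children, samples or measurements are needed.
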